## Abstract

**Background:**

Improving the quality of care for people with dementia and their carers has become a national priority in many countries. Cognitive Stimulation Therapy (CST) groups can be beneficial in improving cognition and quality of life for people with dementia. The aim of the current study is to develop and evaluate a home-based individual Cognitive Stimulation Therapy (iCST) programme for people with dementia which can be delivered by their family carer.

**Methods:**

This multi-centre, pragmatic randomised controlled trial (RCT) will compare the effectiveness and cost-effectiveness of iCST for people with dementia with a treatment as usual control group. The intervention consists of iCST sessions delivered by a carer for 30 minutes, 3 times a week over 25 weeks.

For people with dementia the primary outcome measures are cognition assessed by the ADAS-Cog, and quality of life assessed by QoL-AD. For carers, quality of life using the SF-12 is the primary outcome measure. Using a 5% significance level, comparison of 306 participants will yield 80% power to detect an effect size of 0.35 for cognition as measured by the ADAS-Cog, and quality of life as measured by the QoL-AD. Quality of life for the carer will be measured using the SF-12. The trial will include a cost-effectiveness analysis from a public sector perspective.

**Discussion:**

The UK Department of Health has recently stressed that improving access to psychological therapies is a national priority, but many people with dementia are unable to access psychological interventions. The development of a home-based individual version of CST will provide an easy to use, widely available therapy package that will be evaluated for effectiveness and cost-effectiveness in a multi centre RCT.

## Background

Caring for people with dementia has an enormous impact on health and social care services and on family carers
[1]. The cost of dementia in the UK is over £17 billion a year
[2]. With the number of people living with dementia expected to double in the next thirty years, improving the quality of care for people with dementia and their carers has become a national priority
[1]. In the UK there is growing recognition that psychological therapies for dementia should be more widely available. Indeed the National Service Framework for Older People emphasises the use of non-pharmacological management strategies, such as mental stimulation for dementia, and the UK Department of Health has identified improving access to psychological therapies as a priority
[3].

Cognitive Stimulation Therapy (CST) is an evidence-based approach for people with dementia developed following Cochrane reviews of several psychosocial therapies for dementia, primarily reality orientation (RO)
[4]. RO involves the presentation and repetition of orientation information, such as the date, day and weather
[5]. This may take place intensively throughout the day, or in regular structured group meetings. Benefits of RO noted in the Cochrane review
[4] included improved behaviour and cognition. In addition the need for a more detailed and ongoing programme of orientation activities and large scale multi-centre trials to evaluate this approach was identified. Spector *et al*. found that participating in CST improved quality of life and cognition for people with dementia
[5]. CST may also be more cost-effective than anti-dementia drug treatments
[6]. CST is currently the only non-pharmacological therapy recommended by the National Institute for Health and Clinical Excellence (NICE) guidelines
[7] to improve cognition in people with mild to moderate dementia. A pilot study of an extended programme of maintenance CST found a significant improvement in cognitive function for those receiving maintenance CST, suggesting that benefits could be maintained by weekly sessions for at least 6 months
[8]. Olazaran*et al*. also found that CST groups had long-term cognitive benefits for people with dementia
[9]. The Maintenance CST programme (comprising 14 CST sessions over 7 weeks plus an additional 24 weekly maintenance CST sessions) and accompanying manual have now been further developed as part of the SHIELD study
[10] and evaluated in a randomised controlled trial (RCT). The results of the Maintenance CST trial are expected soon.

The use of group CST is growing rapidly in the UK and internationally, yet many people with dementia may be unable or unwilling to participate in group CST. This could be because they do not want to go out, or because they have restricted mobility or health issues that prevent them from getting out; they may choose not to participate in group-based activities, or groups may not be running in their local area. To assess the acceptability of an individualised CST programme we surveyed care staff attending CST training sessions and carers from the charity *For Dementia*, and we spoke to carers and people with dementia. There was a consensus from people with dementia and family carers that individualised CST should be a high priority because it was likely to be very useful. Comments included 'sounds terrific', 'could bring the carer and person with dementia closer together', 'good for people who won't go out', and 'definitely needed as a useful alternative to medication'. Taken together the evidence suggests that a large-scale trial of iCST for dementia in the UK is feasible, likely to be effective and should be a high priority for research.

Few studies have focused on the use of cognitive stimulation programmes in the home environment. In a pilot study, Moniz-Cook *et al*.
[11] found that a home-based memory management programme involving the family carer led to improvements in memory in the person with dementia, improvements in carer wellbeing, and a reduction in care home admissions at 18 months follow-up. Similar benefits in cognition in people with dementia and carer wellbeing have been reported in studies by Quayhagen*et al*.
[12] and Quayhagen and Quayhagen
[13]. Onder *et al*.
[14] carried out a study of patients with Alzheimer’s disease (AD) taking cholinesterase inhibitors. The intervention consisted of a standardised programme of RO delivered by the family carer in the home for 30 minutes, three times a week over 25 weeks. Alongside training, carers were given a manual, specific schedules for each session, and guidance on how to deliver the sessions. The experimental group receiving the intervention improved relative to the control group on both the Mini Mental State Examination (MMSE) and the Alzheimer’s Disease Assessment Scale – Cognitive subscale (ADAS-Cog).

The primary aim of the proposed trial is to investigate whether individual home-based CST benefits cognition and quality of life in people with dementia and improves carer well-being. Based on previous research findings, we hypothesize that people with dementia receiving iCST will show improvements in cognition and quality of life. A secondary aim of the trial is to explore the costs of those receiving iCST compared to a control group, and to investigate whether iCST is cost-effective.

## Methods

### Design

The design is a multi-centre, single blind, randomized, two-treatment arm (iCST over 25 weeks vs. treatment as usual, or TAU), controlled clinical trial (Figure
1). After recruitment and baseline assessments, pairs of people with dementia and their carer are randomly allocated into either the treatment group (receiving three 30-minute weekly sessions of iCST delivered by the carer for 25 weeks) or control group (receiving treatment as usual for 25 weeks). Primary and secondary measures are completed at baseline (T0) before the iCST programme, first follow-up at 13 weeks after baseline (T1) and second follow-up and primary endpoint at 26 weeks after baseline (T2).

**Figure 1 F1:**
[figure not shown]
Flow of participants through the iCST randomised controlled trial.

### Sample size

Cognition (ADAS-Cog) will be the primary outcome measure. The group CST study by Spector *et al*.
[5] had an effect size (standardised mean difference, or SMD) of 0.32.The Spector *et al*. Cochrane Review of RO
[4] found an SMD of 0.58. The Maintenance group CST study
[8] found an SMD of 0.68 compared to TAU. A recent Cochrane Review of cognitive stimulation found an SMD of 0.37
[15]. Taking a conservative estimate, SMD relative to TAU for iCST is estimated to be at least 0.35. In order to detect an SMD for iCST of 0.35 on the ADAS-Cog with 80% power at a 0.05 (two-sided) significance level, and assuming 15% attrition, a sample size of 306 people with dementia will be required. Experience in previous trials including the CST trial, the needs in care homes trial
[16], and the activities in care homes trial
[17], indicates a 12 to 15% loss to follow-up (7 to 10% excluding deaths) is likely. To safeguard loss to follow-up, standard procedures to maximize the follow-up sample will be applied. These will include regular contact with carers via telephone, letters (for example, reminders for assessment or training appointments) and email, if requested by the carer.

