### Outcome measures

#### Primary outcome measures for the person with dementia

Cognition will be measured using the ADAS-Cog
[25], which consists of 11 tasks assessing disturbances of memory, language, praxis, attention and other cognitive abilities, referred to as the core symptoms of AD, with good reliability and validity
[26].Quality of life will be measured using the Quality of Life Alzheimer’s disease Scale (QoL-AD)
[27] which consists of 13 domains of quality of life. The measure is recommended by the European consensus on outcome measures for psychosocial interventions in dementia
[28].

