#### Primary outcome measures for the carer

Health-related quality of life will be measured using the Short Form-12 Health Survey (SF-12)
[39]. The SF-12 is a comprehensive, psychometrically sound, and efficient measure of health which includes eight concepts commonly represented in health surveys: physical functioning, role functioning, physical pain, general health, vitality, social functioning, emotional and mental health.

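### The sample size section names ADAS-Cog as the one primary outcome, but the abstract and outcome sections also make QoL-AD and SF-12 primary, so the article gives two answers to what decides the trial

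*Protocol article*

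**What the plan says.** The protocol article designates primary outcomes in several places, and they differ.

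- **Sample size:** "Cognition (ADAS-Cog) will be the primary outcome measure", in the singular. The effect sizes from earlier work follow directly. The calculation targets ADAS-Cog, takes a standardised difference of 0.35, and is summed up thus: "with 80% power at a 0.05 (two-sided) significance level, and assuming 15% attrition, a sample size of 306 people with dementia will be required". No other outcome is named in that section.
- **Abstract, Methods:** "For people with dementia the primary outcome measures are cognition assessed by the ADAS-Cog, and quality of life assessed by QoL-AD", and then "For carers, quality of life using the SF-12 is the primary outcome measure". The next sentence applies the 5% level, 80% power and an effect size of 0.35 to both ADAS-Cog and QoL-AD. SF-12 gets a separate sentence with no significance level, power or effect size.
- **Outcome measures:** ADAS-Cog and QoL-AD both stand under the heading "Primary outcome measures for the person with dementia", and SF-12 stands under "Primary outcome measures for the carer".
- **Background, primary aim:** to find out whether iCST "benefits cognition and quality of life in people with dementia and improves carer well-being".

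The Analysis section fixes six months as the primary timepoint but does not say which outcome decides effectiveness. What it leaves to the statistical analysis plan is further definition of the model.

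**The concern.** Which outcome is primary, and what the sample was sized to detect, are matters for the protocol. Here the article answers twice, with different answers, so condensation for a journal does not explain the difference.

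The practical risk is a mixed result. Suppose ADAS-Cog shows no difference at 26 weeks and QoL-AD does. Under the Sample size section the trial has missed its primary outcome. Under the abstract it has met one of two primary outcomes for the person with dementia. Each report could cite the published protocol, and the choice between them could be made after the data are seen.

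The power statement has the same problem. The Sample size section derives its 80% for ADAS-Cog only. The abstract claims it for QoL-AD as well, and nothing in the article supports an SMD of 0.35 on that scale.

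**Working it through.** **Inputs.** From Sample size: SMD 0.35, two-sided 0.05, 80% power, 15% attrition, 306 in total. From Randomisation: 1:1 allocation. Assumed, because the article does not give them: a true SMD of 0.35 on QoL-AD, and a correlation between the two test statistics of 0 to 0.7.

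**1. The plan's own figure.**
- Normal approximation: n per arm = 2 × ((1.960 + 0.842)/0.35)² = 128.1, so 129 per arm and 258 in total; 258/0.85 = 303.5, so 304.
- t-test: 129.1, so 130 per arm and 260 in total; 260/0.85 = 305.9, so 306.
- Power with 130 per arm at two-sided 0.05 is 80.3% (t-test).

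The 306 reproduces for one outcome tested at 0.05.

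**2. Reading A: ADAS-Cog alone decides.** Error 5%, power 80%. Nothing changes.

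**3. Reading B: either ADAS-Cog or QoL-AD suffices, each at 5%.**
- Familywise error, independent tests: 1 − 0.95² = 9.75%.
- Correlated tests (bivariate normal): about 9.5% at correlation 0.3, 9.1% at 0.5 and 8.3% at 0.7.
- Splitting the level to 0.025 each restores 5%. Power per outcome with 260 analysed is then about 71.5% by t-test (71.9% by normal approximation).
- Recovering 80% per outcome at 0.025 takes 156 per arm by normal approximation: 312 analysed, and 312/0.85 = 367.1, so 368 recruited.

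**4. Reading C: both ADAS-Cog and QoL-AD must succeed, each at 5%.** The error rate does not exceed 5%. For power:
- Non-centrality = 0.35 × √(260/4) = 2.82.
- Margin over the critical value = 2.82 − 1.96 = 0.86, so each outcome alone has about 80.6% power (normal approximation).
- Joint power is 0.806² = 65% if independent, 67% at correlation 0.3, 69% at 0.5 and 72% at 0.7.

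**5. Adding SF-12.** If SF-12 were also tested at 5%, in the same family, with any one of three sufficing, the error would be 1 − 0.95³ = 14.3% under independence. The article states neither that level for SF-12 nor that family.

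| Reading | Familywise error | Power, 260 analysed |
|---|---|---|
| A: ADAS-Cog alone | 5% | 80% |
| B: either of two, each at 5% | 8.3% to 9.75% | about 80% per outcome |
| B with 0.025 each | at most 5% | about 71.5% per outcome |
| C: both required, each at 5% | at most 5% | 65% to 72% jointly |

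Of the readings in the table, only A keeps both 5% and 80% with 306 participants.

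**The case against.** A reader might infer that the trial has three primaries, each tested at 5%, and hence an uncontrolled false-positive rate of about 14%. The article does not support that. It attaches 5% to ADAS-Cog and QoL-AD only. The error rate exceeds 5% only if a single success suffices without adjustment, and the article does not say so. SF-12 also answers a question about carers and stands under its own heading, so treating it as a separate family is defensible.

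A reader might also fault the article for not naming an SF-12 score, since it describes a measure "which includes eight concepts commonly represented in health surveys". That choice, like the detail of a multiplicity procedure, may properly sit in the statistical analysis plan, which is not shown. It is not part of this point.

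Nor is the sample size wrong. The abstract's 80% is also arithmetically right for QoL-AD taken by itself, provided the true SMD is 0.35. It misleads only if read as joint power or as resting on evidence for that scale.

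Finally, the Economic evaluation section bases its primary cost-effectiveness analysis on ADAS-Cog and puts QoL-AD among further analyses. This suggests that ADAS-Cog leads. It is evidence of intent, but it concerns the economic analysis and does not undo the primary labels elsewhere.

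These objections limit the size of the problem. They do not remove the conflict in designation, which an unseen analysis plan could not remove from the article either.

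**Conclusion.** The point holds as a contradiction: one primary outcome in the Sample size section against three in the abstract and outcome sections, with the power claim stretched to QoL-AD without a stated basis. It should be corrected because it determines how a mixed result would be read.

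The 306 stands for ADAS-Cog alone. The cost of leaving the matter open depends on the reading: familywise error of about 8.3% to 9.75% if either patient outcome suffices unadjusted, or joint power of about 65% to 72% if both are required. These figures rest on the assumed correlations, and the power figures also on an assumed SMD of 0.35 for QoL-AD. The 14.3% figure is not a finding about this plan, because it needs further assumptions about SF-12.

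**What to change.** Bring the abstract and the outcome sections into line with the Sample size section:

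- ADAS-Cog at 26 weeks is the single primary outcome, tested at two-sided 0.05.
- QoL-AD (person with dementia) and SF-12 (carer) are key secondary outcomes, and their results alone do not establish effectiveness.
- The abstract's 80% power statement refers to ADAS-Cog only.

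A fixed-sequence test of QoL-AD after ADAS-Cog is optional. Making the carer outcome wait for the patient outcomes is not required; given the breadth of the primary aim, that would be a debatable choice.

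If the sponsor prefers to keep QoL-AD as a co-primary, the article should state the success rule, give the basis for the QoL-AD effect size, and restate the power: about 71.5% per outcome at 0.025 each, or about 65% to 72% if both are required, on the assumptions above.

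**Cost.** No extra patients under the first option. QoL-AD and SF-12 lose stand-alone primary status, which sits less easily with the primary aim as worded in the Background. The trial is registered and ongoing, so this is a substantive amendment: the registered outcomes need to be matched to it, and it should be dated and made before any outcome comparison by arm is seen.

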### Analysis

An intention-to-treat analysis will be carried out, in that all available data will be included. A method of multiple imputation using a linear regression model will be used where needed for imputing missing data. The sample size calculations are based on the numbers estimated to be available at the study endpoint, 6 months after randomisation. Analysis of covariance will be used to adjust for baseline differences that may influence outcome variables. Variables to be considered in the model will include, among others, gender and age. Analyses will consider the evaluation 6 months after randomisation as the primary endpoint in evaluating the effectiveness of iCST. Further model definition will be provided in the statistical analysis plan.

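### The planning SMD of 0.35 is presented as a conservative floor although the protocol's own lowest cited effect is 0.32, and the abstract pairs 80% power with the number randomised instead of the number compared

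*Protocol article*

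**What the plan says.** The Sample size section of the protocol article supports the planning effect with four earlier results:

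- The group CST trial "had an effect size (standardised mean difference, or SMD) of 0.32".
- The Cochrane review of reality orientation "found an SMD of 0.58".
- The Maintenance group CST study "found an SMD of 0.68 compared to TAU".
- "A recent Cochrane Review of cognitive stimulation found an SMD of 0.37".

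From these it concludes: "Taking a conservative estimate, SMD relative to TAU for iCST is estimated to be at least 0.35". It then sets the design "with 80% power at a 0.05 (two-sided) significance level", allows for 15% attrition and arrives at 306 people with dementia. It expects a loss of 12 to 15% from experience in previous trials.

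The Analysis section confirms which number the calculation rests on: "The sample size calculations are based on the numbers estimated to be available at the study endpoint". The Methods paragraph of the abstract puts it differently: "comparison of 306 participants will yield 80% power to detect an effect size of 0.35 for cognition".

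**The concern.** Two statements do not agree with the figures around them.

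First, a value described as conservative, and as the least the effect should be, ought not to exceed the smallest effect offered in its support. Here it does. The smallest value is not from a remote comparator either: it comes from a trial of CST, the therapy that iCST adapts.

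Second, the abstract and the main text use 306 for different things. In the main text it is the number before losses. In the abstract it is the number compared.

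At stake is how a null result would be read. A reader told that 80% power was secured for a cautious lower bound will take a non-significant result as stronger evidence against a useful effect than the calculation supports.

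**Working it through.** **Inputs (protocol article).** SMD 0.35; 80% power; two-sided 5% level; 15% attrition, with 12 to 15% thought likely; 306 in total (all Sample size section). Allocation 1:1 (Randomisation section). Lowest cited SMD 0.32 (Sample size section).

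**Step 1: reproduce 306.** The normal approximation is n per arm = 2(1.960 + 0.842)² / d².

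- At d = 0.35: 2 × 7.85 / 0.1225 = 128.1, so 129 per arm and 258 in total; 258 / 0.85 = 303.5, so 304 randomised.
- The two-sample t-test version gives 129.1, so 130 per arm and 260 in total; 260 / 0.85 = 305.9, so **306**, an exact match.

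The stated figure is therefore an unadjusted two-group comparison of about 260 people, inflated correctly for attrition.

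**Step 2: power at 0.35 and at 0.32.** Normal approximation: power = Φ(d√(n/2) − 1.960). The t-test figure uses the noncentral t distribution with noncentrality d√(n/2).

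- Worked case, d = 0.32 and n = 130: 0.32 × √65 = 2.580; 2.580 − 1.960 = 0.620; Φ(0.620) = 0.732.

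| Analysed | SMD | Power, normal | Power, t-test |
|---|---|---|---|
| 260 (15% attrition) | 0.35 | 80.6% | 80.3% |
| 260 (15% attrition) | 0.32 | 73.2% | 72.9% |
| 269 (12% attrition) | 0.32 | 74.7% | 74.4% |
| 306 (no attrition) | 0.32 | 79.9% | 79.7% |
| 306 (no attrition) | 0.35 | 86.5% | 86.2% |

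The smallest SMD with 80% power at 130 per arm is 2.802 × √(2/130) = 0.347, so the design has almost no margin below 0.35.

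**Step 3: what 80% power at 0.32 would take, for scale only.** Normal: 2 × 7.85 / 0.1024 = 153.3, so 154 per arm; 308 / 0.85 = 362.4, so 363 randomised. T-test: 155 per arm; 310 / 0.85 = 364.7, so 365 randomised.

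**Step 4: the abstract.** Taken literally, 306 compared at 0.35 has 86% power (last row of the table). The 80% belongs to about 260 compared (first row). The number and the power in that sentence do not go together.

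**The case against.** The defence is substantial, and most of it stands.

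- **The calculation is correct.** 306 follows from 0.35, and the article never claims 80% power at 0.32. Every design has less power below its planning effect. A reader might infer that the true power is 73% and the stated 80% is an error; the documents do not support that.
- **0.35 is a defensible choice.** It lies below three of the four cited values, below their mean of 0.49 (1.95 / 4) and just below the recent Cochrane review's 0.37. The gap to 0.32 is small beside the standard error of about 0.12 (√(2/130)) that an SMD has with 260 people. This defends the number. It does not defend calling it a floor when a lower value stands in the same paragraph.
- **The 73% is for an unadjusted test.** The Analysis section plans analysis of covariance and leaves the model details to the statistical analysis plan. If the baseline score is a covariate and the SMDs are on the raw-score SD, power at 0.32 would be about 77%, 85% or 95% for a baseline-to-endpoint correlation of 0.3, 0.5 or 0.7. These correlations are assumptions: the article gives none and takes no credit for the gain. So the planned analysis cannot be said to miss an effect of 0.32 more than one time in four; that holds only for the unadjusted calculation.
- **Home delivery.** A reader might infer that a carer-delivered home programme must do less well than groups. The article gives no figure for that, and its Background cites a home-based, carer-delivered reality orientation programme that improved ADAS-Cog relative to control. The point does not rest on this.
- **The abstract is condensed and errs on the cautious side.** Read literally it understates power, and the main text resolves it. It is still a wrong pairing of number and power in the part of the article most often read alone.

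**Conclusion.** Wrong as written, in two places; the sample size itself is sound.

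1. Describing 0.35 as a conservative lower bound is contradicted by the 0.32 cited a few lines before. On the calculation that reproduces 306, power at 0.32 is about 73% (74% at 12% attrition), some 7 points below the figure at 0.35.
2. The abstract's 80% power belongs to about 260 people compared, not 306. A comparison of 306 would have 86%.

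The power figures assume a two-sided 5% two-sample comparison with equal arms, SMDs on the scale of the outcome SD, and no gain from covariate adjustment. They do not show that the trial is underpowered for its planned analysis, nor that it should be enlarged to the 363 to 365 of Step 3; the documents do not give what would be needed to establish either.

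**What to change.** In the Sample size section, delete the words *conservative* and *at least*, present 0.35 simply as the planning value, and add a sentence such as: *306 randomised, about 260 analysed: 80% power for an SMD of 0.35 and about 73% for an SMD of 0.32, before any gain from covariate adjustment.*

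In the abstract, replace the comparison of 306 with the same pair of numbers, 306 randomised and about 260 analysed, for 80% power at 0.35.

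This is a change of wording only. Enrolment, design and analysis stay as they are. The one downside is that the stated power looks slightly less favourable.
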